### **4.3. Criteria for treatment discontinuation or removal from the study**

#### **4.3.1. Withdrawal criteria**

Discontinuation from study is defined as discontinuation of all study visit and examinations. Participants may voluntarily withdraw from the study for any reason at any time. They may be considered withdrawn if they state an intention to withdraw, or fail to return for visits, or become lost to follow up for any other reason. Generally, subjects must be withdrawn from the study for any of the following reasons:

- (1) Subject consent withdrawal.
- (2) Lost to follow-up
- (3) Administration of prohibited medication/treatment/vaccine listed in [Section 6.5.1](#).
- (4) Any pathological event, clinical adverse event, or any change in the subject's status giving indication to the physicians that further participation in the study may not be the best interest of the subject.

These criteria should be checked at each visit subsequent to the first visit and before any study related activity has been conducted. All subjects enrolled will be followed till Day 210. Protocol violations should not lead to subject withdrawal unless they indicate a significant risk to the subject's safety.

If any subject discontinues the study prematurely, the investigator must determine the primary reason for a subject's premature withdrawal and record this information in the medical chart and Off Study Form. For those who are withdrawn due to adverse event(s) or serious adverse event, the event should be followed until resolution or the event is considered stable.

A final safety follow-up conducted through telephone call(s) should be arranged for these subjects as soon as possible. However, for a subject withdrawn within the regular study visit as a reason other than AE, the telephone follow-up could be omitted and no further information has to be collected since last visit (see [Section 5.6](#)). Moreover, for those who are lost to follow-up, investigators should make every effort to contact the subjects and document the steps taken, such as dates of telephone calls, in the source documents.

Subjects who are prematurely withdrawn from the study will not be replaced by an equal number of newly enrolled subjects.

#### **4.3.2. Contraindications to second vaccination**

The following conditions constitute a contraindication to vaccination and those should be

checked prior to second vaccination (at Visit 3 and Visit 4):

(1) Subject with any abnormal laboratory results\* at safety screening visit (Visit 3):

\* Subject with ALT/AST or creatinine  $> 1 \times \text{ULN}$  but  $< 2.5 \times \text{ULN}$  could be re-tested 1 week later.

(2) Pregnancy

(3) Subject with fever defined as oral temperature  $\geq 37.5^{\circ}\text{C}$  at the time before second vaccination.

(4) Subject with acute disease at the time before the second vaccination (defined as the presence of a moderate or severe illness\*\* with or without fever).

\*\* All vaccines can be administered to persons with a minor illness such as diarrhea, mild upper respiratory infection with low-grade febrile illness, i.e. oral temperature  $< 37.5^{\circ}\text{C}$ .

Once a subject meets any of the contraindication, the second vaccination can be administrated at the later day, within a 3-day delay (Day 21 to Day 24), or be withdrawn at investigator's discretion. The investigator should document on the Vaccination page of the CRF, the possible reasons for delay administration/withdrawal (AE, SAE or other) and whether the decision to discontinue further vaccination was made by the subject or the investigator.

Any subject who receive the vaccination with dosage deviation or who does not receive the second vaccination on schedule may not necessarily be withdrawn from the study as further study procedures and the follow-up visits may be performed.

## 5. Study Procedure

This is a phase I, prospective, randomized, open-label, two-center study. A total 60 healthy volunteers will be screened for baseline characteristic inclusion/exclusion criteria after providing a written informed consent. Eligible subjects will be recruited and equally randomized to either receive 2 doses of EV71 vaccine 0.25 ml or 0.5 ml. All subjects should be followed till Day 210. Assessment schedule shown in [Table 5-1](#) lists all study procedures that should be conducted for safety and immunogenicity assessments and the signs "X" indicate when they must be taken place.

**Table 5-1 Study procedures:**

Below is a list of all study procedures through the study period and the signs “X” indicate when the procedures are performed.

|                                         | Screening      | 1 st
vaccination | CPK
monitoring | Safety
screening | 2 nd
vaccination | CPK
monitoring | Follow-up        |                      |                                 |
|-----------------------------------------|----------------|--------------------------------|-------------------|---------------------|--------------------------------|-------------------|------------------|----------------------|---------------------------------|
| Scheduled visit                         | 1              | 2                              | 2a ^   | 3                   | 4                              | 4a ^   | 5                | 6 *       | 7 * /ET # |
| Day                                     | -7~0           | 0
(Baseline)                | 3±1
(D2~4)     | 14+3
(D14~17)    | 21+3
(D21~24)               | 24+3
(D24~27)  | 42±3
(D39~45) | 126±14
(D112~140) | 210±14
(D196~224)            |
| Informed consent                        | X              |                                |                   |                     |                                |                   |                  |                      |                                 |
| Inclusion/Exclusion criteria            | X              | X †                 |                   |                     |                                |                   |                  |                      |                                 |
| Withdrawal criteria                     |                | X †                 |                   | X                   | X †                 |                   | X                | X *       |                                 |
| Contraindication for second vaccination |                |                                |                   | X                   | X †                 |                   |                  |                      |                                 |
| Randomization                           |                | X †                 |                   |                     |                                |                   |                  |                      |                                 |
| Demographics                            | X              |                                |                   |                     |                                |                   |                  |                      |                                 |
| Medical history                         | X              |                                |                   |                     |                                |                   |                  |                      |                                 |
| Physical examination        | X  | X †                 |                   | X                   | X †                 |                   | X                |                      |                                 |
| Oral temperature                        | X              | X †                 |                   | X                   | X †                 |                   | X                |                      |                                 |
| Urine pregnancy test        | X              | X †                 |                   |                     | X                              |                   |                  |                      |                                 |
| Lab (Safety)                            |                |                                |                   |                     |                                |                   |                  |                      |                                 |
| Hematology                  | X              |                                |                   | X                   |                                |                   | X                |                      |                                 |
| Biochemistry                | X              |                                | X ^    | X                   |                                | X ^    | X                |                      |                                 |
| Lab (Immunogenicity)                    |                |                                |                   |                     |                                |                   |                  |                      |                                 |
| IgG titers                              |                | X †                 |                   |                     | X †                 |                   | X                |                      |                                 |
| Neutralizing antibody titers            |                | X †                 |                   |                     | X †                 |                   | X                |                      |                                 |
| Epitope mapping                         |                | X †                 |                   |                     |                                |                   | X                |                      |                                 |
| Vaccination                             |                |                                |                   |                     |                                |                   |                  |                      |                                 |
| Administration                          |                | X                              |                   |                     | X                              |                   |                  |                      |                                 |
| 2-hour observation                      |                | X                              |                   |                     | X                              |                   |                  |                      |                                 |
| 7-day phone contact                     |                | X *                 |                   |                     | X **                |                   |                  |                      |                                 |
| Diary card                              |                |                                |                   |                     |                                |                   |                  |                      |                                 |
| Distribution                            |                | X                              |                   |                     | X                              |                   |                  |                      |                                 |
| Return                                  |                |                                |                   |                     | X                              |                   | X                |                      |                                 |
| Concomitant medications                 | X              | X                              |                   | X                   | X                              |                   | X                | X *       | X *                  |
| Adverse events                          |                | X                              |                   | X                   | X                              |                   | X                | X *       | X *                  |
| Study completion                        |                |                                |                   |                     |                                |                   |                  |                      | X *                  |

 Body height will be only measured at Visit 1.

 Pregnancy test will be only conducted in female subject of childbearing potential.

 Hematology tests include CBC, such as Hb, Hct, RBC count, WBC count, WBC differential and platelet count.

 Biochemistry tests include ALT, AST, γGT, alkaline phosphatase, total bilirubin, total protein, albumin, BUN, creatinine, uric acid, total cholesterol, triglyceride and glucose (fasting).

† These procedures should be conducted before vaccination.

\* These study procedures will be conducted through telephone contact. \*\* For subjects in Block C, a 14-day telephone follow-up will also be taken place. ^ Creatine kinase (CPK) assay at Visit 2a and Visit 4a in Part I should be monitored at the 3rd days after each vaccination, the results should be evaluated by DSMB to decide if CPK should be monitored in Part II.

# ET: early termination (The final telephone follow-up may be omitted if a subject is withdrawn as a reason other than safety.)

All data obtained from those assessments must be supported in the subject's source documentation and entered into the database from separate source documents. For the immunogenicity assessments, the data will be entered through the reports from central laboratory directly.

During the study period, subjects should be seen for all visits on the designated days or within the time window. [Table 5-2](#) shows the Intervals between study visits. It is the investigator's responsibility to ensure that the intervals between visits/contacts are strictly followed.

**Table 5-2 Intervals between study visits:**

| Interval               | Length of interval |
|------------------------|--------------------|
| 1 (Visit 1 → Visit 2)  | Within 7 days      |
| 2 (Visit 2 → Visit 2a) | 3 ± 1 days         |
| 3 (Visit 2 → Visit 3)  | 14 + 3 days        |
| 4 (Visit 2 → Visit 4)  | 21 + 3 days        |
| 5 (Visit 2 → Visit 4a) | 24 + 3 days        |
| 6 (Visit 2 → Visit 5)  | 42 ± 3 days        |
| 7 (Visit 2 → Visit 6)  | 126 ± 14 days      |
| 8 (Visit 2 → Visit 7)  | 210 ± 14 days      |

### 5.1. Visit 1 (Day -7~0) – Screening

At Visit 1, informed consent must be obtained prior to performing any procedures related to the study and after the healthy volunteer has received sufficient information about the study, the opportunity to ask any questions, and consider the options.

Subjects who have been screened should be listed on the Screening Log. Moreover, all screening procedures conducted and the primary reason for not continuing must be documented in the CRF, but no data will be entered into the database for all screened subjects who do not meet criteria for entering the study. No CRF other than the screening part should be completed for these subjects. The following study procedures will be conducted for screening assessments.

- (1) Record date of informed consent signed. Document in the subject's medical chart that he/she is participating in this study, informed consent has been obtained and a copy of the consent has been given to the subject.
- (2) Check inclusion/exclusion criteria.
- (3) Collect the demographic data, including date of birth, age, gender and ethnicity.
- (4) Collect relevant medical history and concurrent diseases. Where possible, diagnoses and not symptoms should be recorded.
- (5) Conduct a complete physical examination including the measurement of weight and height. Measure and record the oral temperature.

- (6) Collect urine samples for pregnancy test (in females of childbearing potential only).
- (7) Collect approximately 8 ml of whole blood sample for following local laboratory tests.
  - Hematological tests: CBC, including Hb, Hct, RBC count, WBC count, WBC differential and platelet count.
  - Biochemistry tests: ALT, AST,  $\gamma$ GT, alkaline phosphatase, total bilirubin, total protein, albumin, BUN, creatinine, uric acid, total cholesterol, triglyceride and glucose (fasting).
- (8) Review prior and concomitant medications. All medications, including vaccine(s), taken during the 30-day period before vaccination should be recorded.

## 5.2. Visit 2 (Day 0) – 1st vaccination

The first dose of study vaccine should be administrated within 1 week after the screening visit. All subjects should complete the following study procedures **prior to vaccination**.

- (1) Check inclusion/exclusion criteria.
- (2) Check withdrawal criteria.
- (3) Conduct randomization of the qualified participant into one of the following dosing groups.
  - **Group A05:** 0.25 ml per dose (5  $\mu$ g total protein + adjuvant 150  $\mu$ g AlPO4)
  - **Group B10:** 0.5 ml per dose (10  $\mu$ g total protein + adjuvant 300  $\mu$ g AlPO4)
- (4) Conduct a complete physical examination with an exception of body height. Measure and record the oral temperature.
- (5) Collect urine samples for pregnancy test (in females of childbearing potential only).
- (6) Collect approximately 7 ml of whole blood sample for following central laboratory tests.
  - Immunogenicity tests: IgG and neutralizing antibody titers, and epitope mapping.

The study vaccine will be administrated intramuscularly (i.m.) in the deltoid of the non-dominant arm. **After vaccination:**

- (1) Observe closely during vaccination and at least 2 hours after vaccine administration. An appropriate medical treatment should be readily available in case of a rare anaphylactic reaction following vaccination.
- (2) Conduct a telephone follow-up 7 days after vaccine administration.
- (3) Dispense thermometer and self-evaluation diary card. Instruct the subjects to monitor body temperature and complete the diary correctly.  
Any solicited symptoms and local and/or general adverse events occurring during a 7 days post-vaccination period, and any unsolicited symptoms occurring during a 21 days post-vaccination period will be recorded on the diary card. The subjects will be instructed to contact the investigator or their delegates immediately if symptoms should manifest or in case of any signs or symptoms occurring which the subject perceives as serious.
- (4) Record concomitant medication(s)/vaccine(s) taken since the previous visit and during vaccination period.

- (5) Record and report adverse or serious adverse event if any one has occurred since the previous visit.

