## 6. Study Drug

### 6.1. Treatment assignment

After the informed consent document is signed, all subjects will be assigned the screening number in turn. Only qualified subjects will be uniquely identified by a combination of a 1-digit center number and a 3-digit subject number. The subject numbers will be given in a consecutive order, i.e. initiate from 001 and subsequently follow by 002, 003... etc. Each subject number will randomly correspond to one of the dosing groups below.

- **Group A05:** 0.25 ml per dose (5 µg total protein + adjuvant 150 µg AlPO4)
- **Group B10:** 0.5 ml per dose (10 µg total protein + adjuvant 300 µg AlPO4)

The corresponding study group of individual subject will be recorded in a sealed envelope. It could be opened only before the first vaccination. Both the subject numbers and corresponding dosage should be recorded on the CRF.

Once a number has been assigned, it could not be replaced by other subject.

This study contains two parts, and there are three and one blocks in Part I and Part II, respectively. The blocks will be initiated in turn as well and the randomization will be conducted for each block separately. For the first part, the first subject enrolled will be assigned to Block A, and the subsequent 2 and 7 subjects will be assigned to Block B and C. After that, the rest 50 subjects will be assigned to Block D for the second part of study (Table 6-1).

Randomization scheme will be created by Qualitix Biostatistics & Data Management (BDM). The first eligible subject, 1-001, will be assigned to low-dose group (Group A05) for the consideration of safety. After that, the allocation of study dosage will be conducted through randomization scheme in order to insure that assignment is unbiased and concealed from subjects and investigator staff.

**Table 6-1** Number of participants assigned to each block:

| Part (Total number)                                                       | Block (Total number)                              | Administration assigned |                    |
|---------------------------------------------------------------------------|---------------------------------------------------|-------------------------|--------------------|
|                                                                           |                                                   | Group                   | Number of Subjects |

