### 7.3.2. Urine pregnancy test

All female subjects except those who have been surgically sterilized (defined as having undergone hysterectomy or bilateral oophorectomy or bilateral salpingectomy; tubal

ligation alone is not considered sufficient) or one year post-menopausal should receive urine pregnancy test. A pregnancy test strip will be used at screening, at Visit 2 prior to randomization and at Visit 4 prior to vaccination. Female with positive result and those who are planning to be pregnant should be withdrawn from this study.

Investigators and their delegates should instruct the females to use medically recognized method of contraception which includes intrauterine contraceptive device; oral contraceptives; diaphragm or condom in combination with contraceptive jelly, cream or foam; Norplant® or DepoProvera® until 2 months after completion of vaccination series.

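### Section 5.2 lists randomisation before the Visit 2 pregnancy test, contradicting 7.3.2, and no section places the Day 0 examination and temperature before randomisation

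*Protocol*

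**What the plan says.** The pre-vaccination list for Visit 2 in protocol section 5.2 opens with its only timing rule: "All subjects should complete the following study procedures prior to vaccination". The items then run: (1) inclusion and exclusion criteria, (2) withdrawal criteria, (3) "Conduct randomization of the qualified participant into one of the following dosing groups", (4) "Conduct a complete physical examination with an exception of body height. Measure and record the oral temperature", (5) urine pregnancy test, (6) blood for immunogenicity.

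Section 7.3.2 gives a different order for the pregnancy test: "A pregnancy test strip will be used at screening, at Visit 2 prior to randomization and at Visit 4 prior to vaccination".

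For temperature, section 7.3.1 requires measurement before the vaccine is given and does not mention randomisation. The dagger footnote to the synopsis flow chart and Table 5-1 likewise ties the marked procedures to vaccination only.

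Section 6.1 keeps the allocation in a sealed envelope that may be opened only before the first vaccination. It does not make opening conditional on completed checks. It adds: "Once a number has been assigned, it could not be replaced by other subject". Section 4.3.1 says: "Subjects who are prematurely withdrawn from the study will not be replaced by an equal number of newly enrolled subjects". Section 6.2 confirms that the study is open-label, and the cohorts in 10.1.1 to 10.1.3 all consist of vaccinated subjects.

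**The concern.** Pregnancy and fever at the time of planned vaccination are exclusion criteria (1) and (3) in section 4.2.2. Inclusion criterion (2) and exclusion criterion (16) rest partly on the investigator's judgment, the former by way of the physical examination. Day 0 pregnancy status and temperature cannot be known until they are measured. A site that works through 5.2 in numerical order would open the envelope first and finish these checks afterwards, with the dose known.

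Two things are at stake. The first is allocation: 6.1 wants assignment to be unbiased and concealed from staff, and a partly discretionary eligibility decision taken with the dose known works against that aim. The second is loss of subjects. A subject who fails a check after the envelope is opened is not replaced, the number cannot pass to someone else, and the subject falls outside every analysis cohort. This matters most in Block B, which holds a single 10 µg subject.

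**Working it through.** **Order of each check, place by place**

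| Check | Position in 5.2 | Timing stated elsewhere | Result |
|---|---|---|---|
| Pregnancy test | item (5), after randomisation at (3) | 7.3.2: before randomisation | contradiction |
| Oral temperature | item (4), after randomisation | 7.3.1 and table footnote: before vaccination | no contradiction; order against randomisation not fixed |
| Physical examination | item (4), after randomisation | 7.3.1 and table footnote: before vaccination | no contradiction; order against randomisation not fixed |

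The envelope rule in 6.1 does not settle the matter, because opening the envelope ahead of the checks still satisfies a limit set only by the first vaccination.

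**Planned numbers.** Table 6-1 gives A05: 1 + 1 + 3 + 25 = 30, and B10: 0 + 1 + 4 + 25 = 30. The total is 60, which reproduces the stated size and 1:1 ratio. Section 10.6 gives no power calculation to reproduce.

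**Size of the loss.** The protocol gives no Day 0 failure rate, so p is an assumption, shown over a range. Expected losses are 60p. The chance of at least one loss is 1 − (1 − p)^60. The chance of losing the only Block B 10 µg subject is p. The chance of losing either Block B subject is 1 − (1 − p)^2.

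| Assumed p | Expected losses of 60 | At least one of 60 | Sole Block B 10 µg subject | Either Block B subject |
|---|---|---|---|---|
| 1% | 0.6 | 45% | 1% | 2.0% |
| 2% | 1.2 | 70% | 2% | 4.0% |
| 5% | 3.0 | 95% | 5% | 9.8% |

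Subject 1-001 is assigned to A05 and not randomised, so strictly 59 subjects are exposed. Expected losses are then 59p = 0.59, 1.18 and 2.95, which changes nothing material.

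**Effect on precision.** Section 10.3.2 plans 95% confidence intervals for adverse event percentages. Taking the exact two-sided interval as an assumption, the upper limit for zero events is 1 − 0.025^(1/n):

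- n = 30: 11.6%
- n = 29: 11.9%
- n = 27: 12.8%

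Even if all three losses expected at p = 5% fell in one dose group, its upper limit would rise by only 12.8 − 11.6 = 1.2 percentage points.

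**The case against.** The strongest reply is that the numbering in 5.2 is not a sequence. Nothing in 5.2 calls it one, and other lists in the protocol are plainly not in time order. Visit 1 puts the criteria check before the history, examination and tests that decide it. Visits 3 and 4 put the contraindication check before the measurements it needs. After vaccination at Visit 2, item (2) is "Conduct a telephone follow-up 7 days after vaccine administration", ahead of dispensing the diary the same day. In addition, item (1) is the criteria check, item (3) is addressed to a qualified participant, and 6.1 gives a subject number only to qualified subjects. On that reading eligibility is settled before randomisation.

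Much of this stands. A reader might infer that the protocol tells sites to randomise subjects who have not been shown to qualify; the text does not go that far. But the reply does not remove the problem. If the list is a sequence, item (1) precedes the measurements it depends on. If it is not, the list gives no assurance that those measurements precede randomisation. For the pregnancy test, 7.3.2 states an order that 5.2 reverses.

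It is also fair to say that fever is a numeric cut-off and pregnancy a strip result, so only the examination leaves real room for discretion. The primary analysis is descriptive, so no between-dose test is biased. Every subject will have been examined and, where applicable, tested at screening within the previous 7 days. These points limit the size of the concern.

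**Conclusion.** The point holds as one contradiction (the pregnancy test, 5.2 against 7.3.2) and one badly fixed order (examination and temperature against randomisation). A reader might infer that 7.3.2 is breached for all three checks. It is not, because 7.3.2 covers the pregnancy test alone, and that test applies only to females of childbearing potential.

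The practical effect is probably small. The figures of 0.6 to 3 subjects rest wholly on assumed failure rates of 1% to 5% and on sites following the list as numbered. The 45% to 95% chance of at least one loss should not be read as serious damage to the trial, since the confidence limits hardly move. The sharper consequence is in Block B: losing its 10 µg subject is unlikely (1% to 5%) but would leave no 10 µg data before Block C, where four more subjects receive that dose. A reader might infer that Block C would then open regardless. The protocol does not say so: section 3.1 requires the investigator to confirm the initial safety of the prior block, and no section addresses a Block B subject who was randomised but not vaccinated.

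The correction is worth making because it protects the allocation at almost no cost.

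**What to change.** In section 5.2, list randomisation after the Day 0 physical examination, oral temperature and pregnancy test, which brings it into line with 7.3.2. In section 6.1, state that the envelope is opened only after all Day 0 eligibility checks are passed.

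The cost is one reordered list and one added sentence. No procedure is added, and the planned 30 + 30 is unchanged. The rows of the flow chart and Table 5-1 need no reordering: they are not chronological (randomisation, done at Visit 2, sits above demographics and medical history, collected at Visit 1).
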